#### Home-monitored group details

The women included in the home monitored group are women who met the inclusion criteria (Table 1). They were recruited to the study from 2024, following the final regulatory study approvals and integration of the technical home monitoring and reporting devices into the hospital electronic patient journal (EPJ) system. These women will be provided a training session with the research midwife in order to operate the medical devices they will use during home monitoring. The training will be conducted using standardized written and oral instructions relevant for the main diagnostic groups (e.g., hypertension or pPROM). The personalized follow-up plan includes instructions for how to contact the hospital 24/7 and how to be admitted when needed.

During home monitoring, women will respond to a checklist (Supplementary 1) on an application (app) (MyDignio). This eHealth application will be downloaded to the patient's smartphone during their hospital stay. The app has a direct connection to the electronic patient journal system at the hospital. Dignio Connected Care is approved by the South-Eastern Norway Regional Health Authority (the region where the HOME study is carried out) as a device for general patient home monitoring in the region. The researchers in the HOME study have developed relevant questions about symptoms and objective measures of the pregnant woman's health according to the indication for inclusion (e.g., pPROM or hypertensive disorders of pregnancy) (Supplementary 1).

The women included in the home monitoring group due to hypertensive pregnancy disorders will be asked questions in the app about symptoms related to increased severity of the disease (e.g., headache, swelling, epigastric pain, visual symptoms, fetal movements) and asked to enter their blood pressure values (recorded with a validated blood pressure device available for this study from the hospital) and results from the urine protein test.

For women included in the home monitoring group due to pPROM, the MyDignio app includes questions related to infection and premature birth (e.g., fever, pain, amniotic fluid color, and fetal movements), and objective markers of infection and fetal wellbeing signs are registered [e.g., temperature recording (measured using a study-provided device) and C-reactive protein test (CRP)]. According to hospital guidelines, vaginal and urine tests for bacterial infection will be performed before the start of home monitoring.

The women included due to previous adverse obstetric events will be asked questions about fetal movements in the MyDignio app. They may also be assigned a mix of questions from the other described risk groups, as indicated by the senior obstetrician.

The study-specific feedback given to the patient in the MyDignio app in response to the registered answers and registrations of symptoms and signs are detailed in Supplementary 1. The home-monitored group is, in addition to daily MyDignio app reports, instructed to perform CTG (see details below) according to the clinical indications set by the senior obstetrician. Many home-monitored patients will also be scheduled for an ultrasound investigation once a week at the hospital to assess fetal wellbeing and growth and amniotic fluid volume. Women with pPROM will, in addition, be scheduled for vaginal and urine testing of bacterial infection and infection status (CRP and leucocytes) and CTG at individually assigned intervals. Likewise, women with hypertensive disorders will be scheduled for blood samples and urine testing (until proteinuria is established) at individually assigned intervals.

#### Technological solutions for telemonitoring

The technological solutions for registering clinical data during home monitoring include the Nemo healthcare system (Veldhoven, the Netherlands) for home CTG monitoring. In addition, a web-based communication platform will be used by the home-monitored women (Dignio Connected Care, Norway) (10), which is accessible by the women through MyDignio (for patient symptoms and clinical signs) and by the healthcare providers (through DignioPrevent). Both systems are European conformity (CE)-licensed medical devices. The Nemo healthcare system has been evaluated as acceptable by users and has been found to improve telemedical understanding (11).

The home-monitored patients in the present study will record CTG at individually assigned intervals with an electrocardiogram-based device placed on the abdomen (Nemo Fetal Monitoring System), recording fetal heart rate patterns, uterine contractions, and maternal pulse. The signals are sent wirelessly to a CTG-receiver (a tablet; iPad, Apple) that transfers the signals through an encrypted data channel to the Milou Real-Time Server software (Medexa, Sweden). The CTG traces are visually interpreted by healthcare professionals at the hospital, according to international guidelines (12). These fetal and uterine signals are not visible on the user’s iPad screen (the pregnant woman), and are only visible to the healthcare staff at the hospital. Two recent studies have, after the planning of the HOME study, concluded that the use of such a home CTG system is feasible for women with pregnancy complications (5, 6).

The Microlife WatchBP Home monitor used in the present study has been found to be valid for monitoring blood pressure in the general and the pregnant populations (13–15). Appropriate cuff widths are used according to arm circumference (13). For women with pPROM, CRP is analyzed at home by the woman using the QuickRead go Instrument, which has shown acceptable agreement with reference methods (16, 17). Rectal temperature is measured by the Microlife MT 800 Digital Thermometer.

### Outcome measures

The primary outcome variable is a composite of severe adverse events, as detailed in Table 2. These include maternal mortality, severe maternal morbidity/organ damage [e.g., sepsis, eclampsia, cerebral hemorrhage, acute respiratory distress syndrome, liver rupture, pulmonary embolism, amniotic fluid embolism, hemolysis, elevated liver enzymes, and low platelets (HELLP), HELLP without hemolysis (ELLP), and/or disseminated intravascular coagulation (DIC)], and fetal or early neonatal death. The primary composite outcome will be thoroughly evaluated by the Diagnostic Advisory Group (DAG). The members of the DAG include three senior obstetricians, one senior pediatrician, and one experienced midwife, all of whom are employed at Oslo University Hospital but are unrelated to and independent of the study group members and principal investigator (PI). All separate primary outcome events will be presented to the DAG, who will discuss and evaluate whether the events are related to the study or not, and whether the events could have been prevented or not.

**Table 2 T2:** Description of the clinical outcome variables of the HOME study.

Variable category	Variable	Definition/description	Evaluated by the Diagnostic Advisory Group
Primary composite outcome	Maternal death (direct)	Maternal death during pregnancy until 42 days postpartum due to pregnancy complications	Yes
	Severe maternal morbidity/organ damage	• Sepsis • Eclampsia • Cerebral hemorrhage • Acute respiratory distress syndrome • Liver rupture • Pulmonary embolism • Amniotic fluid embolism • HELLP (hemolysis, elevated liver enzymes, low platelets)/ELLP (HELLP without hemolysis) • DIC (disseminated intravascular coagulation)	
	Fetal/neonatal death	Intrauterine fetal death or death first 4 weeks after birth	
Secondary maternal outcomes Secondary offspring outcomes	Chorioamnionitis	Clinical diagnosis	No
	Malignant hypertension	Persistent systolic blood pressure ≥160 mmHg and/or diastolic blood pressure ≥100 mmHg	
	Adverse neonatal outcome	*Apgar* score <7 at 5 min of age *Umbilical cord acidemia* (arterial pH ≤7.10) *Metabolic acidosis* (umbilical artery pH <7.00 combined with base deficit in the extracellular fluid ≥12 mmol/L) (18)	
	Neonatal intensive care unit	Days	
	Respirator/ventilation support treatment	Days	

The secondary study outcomes (Table 2) include maternal morbidity [chorioamnionitis and malignant hypertension (persistent systolic blood pressure ≥160 mm Hg and/or diastolic blood pressure ≥100 mmHg)] and adverse neonatal outcomes (Apgar score <7 at 5 min, cord acidemia, metabolic acidosis (18), admission to neonatal intensive care unit, and/or respirator/ventilation support treatment). Umbilical cord acid-base data will be validated according to the method described by Kro et al. (19, 20).

In addition to the daily reports, the patient-reported outcome measures in the HOME study will be collected by digital questionnaires sent to the study participants' smartphones 2–7 days after hospital admission or start of home monitoring, and again at 10–12 weeks postpartum, for study group comparison. One digital reminder will automatically be sent to non-responders. The validated questionnaires include the Bergen Insomnia Scale (21), the General Perceived Self-Efficacy Scale (22), Sense of Coherence-13 (23), Edinburgh Postnatal Depression Scale (24–26), and the 25-item version of the Hopkins Symptom Checklist (27, 28). In addition, explanatory variables for multivariable analyses will be added, including a history of depression (based on DSM-IV criteria) (26, 29) and major life events during the previous 12 months, including serious events related to marriage, family, friends, work, or health (26), selected from established life event scales (26, 30, 31). In addition, a few HOME study-specific questions/items were constructed for the particular study that are not validated. After completing the questionnaires, the participants will be informed about available help resources if they are in need of further mental support during a potentially demanding period in their life (e.g., from their primary healthcare provider or a Norwegian mental health organization that is available 24/7).

The cost of home monitoring will be compared to hospital monitoring, including the maternal costs until delivery, but excluding maternal and newborn healthcare costs after delivery. The health economics assessment will evaluate hospital costs, including costs related to health professionals and administrative personnel time, for both outpatient and inpatient care. The mean cost per outpatient consultation and inpatient hospital cost per day will be calculated. The estimated mean cost is multiplied by the number of registered contacts at different departments during the study time (until delivery). Using the overhead indirect cost method, we will calculate the average estimated mean cost for different wards where the patient has a registered contact at the Oslo University Hospital. All costs will be evaluated as if operating under steady-state conditions based on the budget of 2023. Prices will be converted from Norwegian crowns (NOK) to U.S. dollars (US$) using the mean exchange rate for 2023 of 1 US$ = 9.86 NOK. All patient costs will be covered by the Norwegian public insurance system.

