Recent technological development has generated new opportunities for health surveillance outside the hospital, i.e., at home. Home monitoring systems for high-risk pregnancies, with the opportunity for patient registration of CTG, have not been tested or established in most countries, including Norway. After the planning of the home monitoring of high-risk pregnancies (HOME) study, two articles reporting on outcomes after home monitoring of high-risk pregnancies have been published: one retrospective study of 8 years of practice in Denmark (5) and one randomized controlled trial from the Netherlands (6). Both concluded that home monitoring may be a safe alternative to inpatient hospital care for selected women with high-risk pregnancies. Home monitoring of blood pressure in pregnancy poses challenges, as blood pressure can rise rapidly during pregnancy. Monitoring of blood pressure at home in pregnant women with gestational hypertension has, however, demonstrated better compliance with guidelines, likely lowering the burden on public health resources (7).

Any change in clinical practice needs to be thoroughly evaluated, including an evaluation of clinical outcomes. Thus, in this study, clinical safety, patient-reported outcomes, and healthcare economics following the introduction of home monitoring in high-risk pregnancies will be investigated. Ultimately, personalized follow-up with more telemonitoring opportunities and flexibility may enable the much in-demand specialist resources at obstetric departments (e.g., midwives and obstetricians) to focus on the patients with the greatest need for in-hospital follow-up.

The hypothesis in this clinical study is that home monitoring in selected high-risk pregnancies does not increase the risk of severe adverse maternal or fetal outcomes for women and their fetuses compared to similar pregnancies being followed up through hospitalizations and/or frequent outpatient visits. We also anticipate increased patient-reported satisfaction in line with positive patient expectations from general technology-enabled care solutions (8) and findings from our own preclinical expectation study related to the HOME study (9). Finally, we expect that the freeing up of hospital beds will reduce hospital costs and thereby result in a positive health economic assessment, despite the increased device costs and reorganization of the hospital’s follow-up system.

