### Data analysis

After inclusion in the study, baseline data such as patient demographics, medical and obstetric history, and pregnancy data will be collected and registered in a case report form before entering and coding the data in a study-specific electronic record. After delivery, the remaining relevant data for the assessment of maternal mortality and morbidity and perinatal outcomes will be collected from the hospital's electronic patient journal and registered in the study-specific HOME records. All primary and secondary outcome data will be registered, in addition to gestational age at birth and birthweight (Table 2).

The composite primary outcome will be analyzed using logistic regression analyses. Parity and gestational age will be included as potential confounding variables. Further, each component of the composite primary outcome and all secondary outcomes will be analyzed to provide further insight into the research question. The results will be presented as odds ratios with 95% confidence intervals, in addition to crude proportions (not adjusting for parity and gestational age).

The obstetric experts in the DAG will independently evaluate all composite primary outcomes continuously throughout the project period and without interference from anyone in the project group. The DAG will conclude whether any primary (severe adverse) outcomes are related to the study or not, and the results will be presented in detail in the study report.

The study participants' experience, mental wellbeing (depression and anxiety), sense of coherence, and self-efficacy will be described at the group level (hospital monitoring vs. home monitoring) at the two investigated time points (2–7 days after hospital admission or start of home monitoring and again at 10–12 weeks postpartum).

The cost-effectiveness of home monitoring compared to the hospital-monitored group will be described at the group level based on the estimated cost of each admission to different wards at Oslo University Hospital and outpatient visits from inclusion in the HOME study until delivery.

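### The economic comparison covers only maternal hospital costs up to delivery, so it supports a statement about antenatal cost but not about cost-effectiveness or overall hospital cost

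*Protocol article*

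**What the plan says.** The costing rule is in the protocol article under Outcome measures. The comparison takes in maternal costs up to delivery, "excluding maternal and newborn healthcare costs after delivery". The unit costs are described as follows: "The mean cost per outpatient consultation and inpatient hospital cost per day will be calculated". They are multiplied by the contacts registered up to delivery, with an overhead method and the 2023 budget of Oslo University Hospital. The Data analysis section repeats the window, counting ward admissions and "outpatient visits from inclusion in the HOME study until delivery".

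The label and the expected conclusion are wider than that window:

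- Data analysis: "The cost-effectiveness of home monitoring compared to the hospital-monitored group will be described at the group level".
- Introduction: "we expect that the freeing up of hospital beds will reduce hospital costs and thereby result in a positive health economic assessment".
- Abstract: the service is expected to have lower economic costs.

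Neonatal resource use is collected, but only as a clinical outcome. The secondary outcomes include "admission to neonatal intensive care unit, and/or respirator/ventilation support treatment", and Table 2 records both in days. Gestational age at birth is also registered. The article gives none of these a role in the economic analysis.

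**The concern.** The costing window closes at an event that monitoring may move. The Introduction says that surveillance is meant to improve the timing of delivery, and that preterm premature rupture of membranes, one of the inclusion groups, carries a risk of preterm birth. If the groups differ in delivery timing or in neonatal care, the window has two effects. Antenatal contacts cut off by delivery lower the recorded cost, and any neonatal intensive care that follows adds nothing.

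A difference between the groups is plausible. Women are not randomised, and most hospital-monitored women were recruited before home monitoring began.

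At stake is what the economic result can be used for. The Discussion says it should help hospitals judge the cost of implementing the service. Neonatal intensive care is a hospital cost, so a reader who meets the term cost-effectiveness, or a statement of lower hospital costs, would assume that it had been counted.

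**Working it through.** The plan states no figure for the cost comparison, so there is none to reproduce. The sample size concerns the composite primary outcome and does not bear on this point. The check applies the stated rule, recorded cost = unit cost × contacts or days until delivery, to illustrative cases.

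**Inputs**

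- From the article: inpatient care is costed per day and outpatient care per consultation; newborn care has no cost; many home-monitored women attend ultrasound once a week; 125 women are planned per group.
- Assumed, because no unit costs are given: one antenatal ward day = 1 unit; one neonatal intensive care day = *r* units, with *r* = 1, 2 or 4; one outpatient consultation = *c* units, with *c* no more than 1.
- Varied: delivery *k* = 7 days earlier; *m* = 0, 3 or 7 additional neonatal intensive care days.

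**Step 1: a woman who would have stayed an inpatient.** The planned window records −*k* = −7 units, whatever *m* is. With newborn care counted, the change is −*k* + *m* × *r*:

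| *m* | *r* = 1 | *r* = 2 | *r* = 4 |
|---|---|---|---|
| 0 | −7 | −7 | −7 |
| 3 | −4 | −1 | +5 |
| 7 | 0 | +7 | +21 |

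The sign reverses once *m* exceeds *k*/*r*, which is 7, 3.5 or 1.75 days.

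**Step 2: a woman monitored at home.** A day at home is not a ward day. With weekly ultrasound as the only visit, 7 days is 7/7 = 1 lost contact. The planned window then records −*c*, at most 1 unit against 7 for the inpatient. With newborn care counted, and *c* at its upper limit of 1, the change is −1 + *m* × *r*:

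| *m* | *r* = 1 | *r* = 2 | *r* = 4 |
|---|---|---|---|
| 0 | −1 | −1 | −1 |
| 3 | +2 | +5 | +11 |
| 7 | +6 | +13 | +27 |

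Tests at individually assigned intervals, readmission, or remote reviews counted as contacts would raise the antenatal part. For this woman the antenatal saving is small, and the main gap is the uncosted newborn care.

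**Step 3: the group comparison.** Let *d* be the difference in mean neonatal intensive care days per woman, home minus hospital. The planned comparison leaves out *r* × *d* units per woman. For *d* = +1 that is 1, 2 or 4 units per woman, or 125 × 1 = 125, 125 × 2 = 250 or 125 × 4 = 500 ward-day equivalents over a group of 125. For *d* = −1 the same amounts apply in the other direction, and home monitoring would look dearer than it is. For *d* = 0 nothing is lost. The article gives no information on *d*.

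**The case against.** The strongest reply is that this is a declared scope. The exclusion of later costs is stated openly and repeated consistently, so the plan does not contradict itself on the window. The economic hypothesis also concerns beds freed, set against device and reorganisation costs, which are costs of antenatal surveillance. Both points stand: antenatal hospital cost is a legitimate quantity. They do not cover the wider label or the wider expected conclusion.

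A reader might go further and infer that the plan rewards poor home monitoring, because early delivery at home would be booked as a week of ward days saved. The documents do not support that. A home-monitored woman delivered early loses mainly outpatient contacts. Ward days are cut off mostly in the hospital group, where this lowers the hospital group's cost and works against home monitoring.

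Nor would harm be hidden. Neonatal intensive care and ventilation days are secondary outcomes analysed between the groups, so a cheaper group with more neonatal days would be visible. That also stands, although the reader would have to weigh the two results without a common unit.

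Finally, adding neonatal stays brings case-mix differences into a non-randomised comparison and widens the interval. This is a reason to add them as a sensitivity comparison and leave the planned one in place.

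**Conclusion.** The point holds as a matter of scope and labelling, with a real but unquantified risk of a misstated difference in overall hospital cost. The plan costs maternal contacts up to delivery, gives newborn care no cost, and uses a term and an expected conclusion that reach further.

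The size rests wholly on assumptions. At 1 to 4 ward days per neonatal intensive care day, each day of group difference per woman omits 1 to 4 ward-day equivalents per woman, in either direction. If delivery timing and neonatal care turn out alike in the two groups, the omission does not affect the comparison.

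It would be too strong to say that no cost conclusion can be drawn, or that the window favours home monitoring. A conclusion on antenatal hospital cost can be drawn, and the documents do not fix the direction of any distortion.

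**What to change.** 1. Keep the planned comparison and call it antenatal hospital cost. Drop the term cost-effectiveness for it.
2. Add a sensitivity comparison that also costs the neonatal intensive care days already recorded in Table 2, using a cost per day for that ward from the same overhead method and 2023 budget.
3. Enter ventilation days only as a supplement to the intensive care day. The two probably overlap, and no day should be costed twice.
4. Claim lower overall hospital cost only if both comparisons support it. If only the first does, report lower antenatal hospital cost and say so.

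The price is one more unit cost and one more table, with no new patients, visits or data items. A few long neonatal stays will widen the interval. The unit costs will still come from Oslo University Hospital alone although Drammen Hospital also recruits, which should be stated with the result.

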## Materials and methods

### Study setting

The observational HOME study has been carried out in southeastern Norway, primarily at Oslo University Hospital (OUH) in Norway's capital, Oslo, which has the largest Obstetric Department in Norway, with 8,000 deliveries annually. Another hospital in the region, Drammen Hospital, with 2,000 deliveries annually, will also recruit some patients to the study.

Norway offers pregnant women free-of-charge antenatal, delivery, and postpartum care. Women deemed at high risk for adverse pregnancy outcomes, either due to current pregnancy complications or previous adverse obstetric outcomes, are offered intensified follow-up according to a national expert guideline (3).

The observational study protocol for this study was posted on ClinicalTrials.gov in 2023 (10 March 2023: ref: NCT05763069). The first woman was recruited to the hospital-monitored group in December 2022. The first woman monitored at home was recruited in June 2024, following a 2-year period of study adaptation due to General Data Protection Regulation (GDPR) issues and technology solution developments for the transfer of home-registered data to the hospital's electronic patient journal systems.

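### The stated costing rule has no term for home devices, consumables, platform or remote review, which tilts the cost comparison toward a saving

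*Protocol article*

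**What the plan says.** The health-economics paragraph under Outcome measures sets out to compare the cost of home monitoring with that of hospital monitoring, up to delivery. It builds the costing as follows:

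- **Scope:** hospital costs, "including costs related to health professionals and administrative personnel time, for both outpatient and inpatient care".
- **Unit costs:** "The mean cost per outpatient consultation and inpatient hospital cost per day will be calculated".
- **Volume:** "The estimated mean cost is multiplied by the number of registered contacts at different departments during the study time (until delivery").
- **Overhead:** "we will calculate the average estimated mean cost for different wards where the patient has a registered contact at the Oslo University Hospital".
- **Price base:** "All costs will be evaluated as if operating under steady-state conditions based on the budget of 2023".

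Data analysis restates the comparison as a group-level description "based on the estimated cost of each admission to different wards at Oslo University Hospital and outpatient visits" from inclusion until delivery.

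Two other statements bear on this. The Introduction expects a positive economic result "despite the increased device costs and reorganization" of the follow-up system. Study setting reports that "The first woman monitored at home was recruited in June 2024".

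**The concern.** A home-monitored woman uses resources that a hospital-monitored woman does not. The sections Home-monitored group details and Technological solutions for telemonitoring list them: a home CTG system with tablet and server software, a communication platform, a blood-pressure monitor, a home CRP instrument and a thermometer for women with pPROM, daily app reports, and hospital staff who read the CTG traces. The costing rule has places for inpatient days and outpatient consultations, but no stated place for these items.

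The gap is one-sided. Costs missing from one group only do not cancel in a difference. Here they would lower the home group's total and enlarge the apparent saving. The Introduction names device and reorganization costs as what the saved bed-days must outweigh, so a rule without those costs does not fully test the stated expectation. Cost is one of the three things the study sets out to evaluate, and the Discussion says the results should help hospitals decide on implementation.

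**Working it through.** The documents give no cost total, unit price or expected saving, so there is no figure to reproduce. The check sets the statements side by side and then illustrates sensitivity on assumed inputs.

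**1. Home-group resources against the rule**

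| Resource (where described) | Stated place in the costing rule |
|---|---|
| Home CTG system, tablet, server software; blood-pressure, CRP and temperature devices (Technological solutions) | None |
| Consumables for home testing (implied by home urine and CRP tests) | None |
| Platform and app (Home-monitored group details; Technological solutions) | None |
| Staff reading CTG traces and app reports (same sections) | None named; possible if registered as an outpatient contact |
| Training session (Home-monitored group details; User involvement) | None named; partly inside an inpatient day, because training is planned while the woman is still in hospital |
| Hospital visits and readmissions | Covered |

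**2. Price base.** Unit costs rest on the 2023 budget and the first home-monitored woman was recruited in June 2024. No study participant was monitored at home in the budget year. The text does not explain how ward overhead from that year would carry the running cost of the service.

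**3. Units.** Outcome measures defines a cost per inpatient *day* but multiplies by *contacts*; Data analysis speaks of the cost of each *admission*. For one stay of d days at day cost c, the day reading gives d × c. A literal contact reading, with the stay as one contact, gives c. The readings agree only when d = 1. The contact reading would understate long stays, so this ambiguity is separate from the omission and need not push in the same direction. Step 4 takes the day reading.

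**4. Illustration. Every input is an assumption.** Take one inpatient day as 1 unit and an outpatient visit as v = 0.3. Let D be monitored days, f the share of them moved home, V the extra visits in the home group, and h the uncosted home-service cost per home day.

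- Contact-only saving: S = D − [D(1 − f) + V × v] = D × f − V × v
- Omitted cost: h × D × f
- Share of the apparent saving that is omitted cost: h × D × f / S
- Value of h at which the saving disappears: S / (D × f)

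| D, f, V | D × f | S | h = 0.10 | h = 0.25 | h = 0.50 | Break-even h |
|---|---|---|---|---|---|---|
| 14, 0.8, 2 | 11.2 | 11.2 − 0.6 = 10.6 | 1.12/10.6 = 10.6% | 2.8/10.6 = 26.4% | 5.6/10.6 = 52.8% | 10.6/11.2 = 0.946 |
| 14, 0.5, 2 | 7.0 | 7.0 − 0.6 = 6.4 | 0.7/6.4 = 10.9% | 1.75/6.4 = 27.3% | 3.5/6.4 = 54.7% | 6.4/7.0 = 0.914 |
| 7, 0.5, 1 | 3.5 | 3.5 − 0.3 = 3.2 | 0.35/3.2 = 10.9% | 0.875/3.2 = 27.3% | 1.75/3.2 = 54.7% | 3.2/3.5 = 0.914 |

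In these scenarios the share depends mainly on h and hardly on length of stay. The documents do not allow h to be estimated.

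**The case against.** The best defence is that the article nowhere excludes home-service costs. The paragraph opens by making the cost of home monitoring an object of the comparison, and its scope sentence uses the open word *including*. An article may also leave an itemised cost list to the full protocol. Three stronger conclusions that a reader might draw are therefore not supported:

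- **That the home service is counted as zero.** No sentence says so. User involvement describes training before discharge, which may fall inside a costed inpatient day. It also says staff protocols cover the choice of existing reimbursement classifications, so remote contacts may be registered and costed as outpatient contacts.
- **That a 2023 base cannot contain the service.** Costs are to be valued as if in steady state, so 2023 can be read as a price level applied to a hypothetical service. The dates show that no participant was monitored at home that year. They do not show that home items cannot be priced on that base.
- **That a saving cannot be refuted by this method.** It can. Many home-monitored women will have weekly ultrasound and other scheduled tests, and they can be admitted. If their contact costs do not fall, the expected saving fails even with no device costs. The method is tilted, not closed.

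It is also fair to say that cost is a secondary outcome and does not touch the primary safety conclusion.

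What does not stand is the reading that this is only condensed reporting. The article fixes scope, unit costs, volume, overhead method, budget year and even the exchange rate, and Data analysis repeats the same base of admissions and visits. Even if every remote contact were coded as an outpatient visit, devices, consumables and the platform licence would still have no stated entry, and a 2023 outpatient unit cost is not shown to reflect remote review.

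**Conclusion.** The concern holds as a flaw in a stated rule. As written in both places, the costing names no component for home devices, consumables, platform licence or remote review, although the Introduction expects device and reorganization costs to rise. Followed literally, it omits costs that fall only on the home group and so biases the comparison toward a saving.

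The direction of this omission is clear, given that inpatient day costs are multiplied by days. Its size cannot be derived from the documents. The 11% to 55% range rests wholly on assumed values of 0.10 to 0.50 of an inpatient day per home day, and would shrink to the extent that training and remote contacts are already captured. The day, contact and admission wording is a smaller inconsistency that should be settled at the same time. The change should be made, but nothing here affects the primary safety analysis.

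**What to change.** In Outcome measures, add an explicit home-service cost component made up of annualised devices, consumables, the platform licence, and remote-review time not already registered as a contact (to avoid double counting). Price it in 2023 NOK, so that it shares the base of the ward costs, and charge it per home-monitoring day. If some of these items are already captured, say where.

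State that the inpatient day cost is multiplied by inpatient days and the outpatient cost by consultations, and use the same units in Data analysis.

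The cost is small: procurement figures that the department should hold, an estimate of remote-review time, and revised wording. No patient procedure changes. The downside is a little extra costing work and probably a less favourable cost figure for home monitoring.
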